# Study Enrollment and Withdrawal

The study population will be drawn from children who are brought to the Ndirande Health Centre and are found to have uncomplicated malaria. Six hundred forty children will be enrolled. We expect enrollment to occur over an 18-month period so the entire study duration will be two to two and a half years, but the duration for each participant will be one year.

## Subject Inclusion Criteria

Participants must meet all of the following inclusion criteria to be eligible to participate in this study.

- Subjects aged >6 months to 5 years presenting to Ndirande Health Centre with signs or symptoms consistent with malaria including, but not limited to, one or more of the following:
  - fever at the time of evaluation (axillary temperature > 37.5oC by digital thermometer)
  - report of fever within the last two days
  - clinically profound anemia (conjunctival or palmar pallor)
  - headache
  - body aches
  - abdominal pain
  - decreased intake of food or fluids
  - weakness
- Weight≥ 5kg
- Positive malaria smear for *P. falciparum* mono-infection with parasite density 2,000-200,000/mm3.
- Planning to remain in the study area for 1 year
- Willingness to return for four-weekly routine visits, as well as unscheduled sick visits
- Parental/guardian consent for each participant

### Rationale for Inclusion Criteria

*Subjects aged >6 months to 5 years presenting to Ndirande Health Centre with signs or symptoms consistent with malaria.* This group is the target population recommended by the WHO protocol and this age group carries the highest burden of symptomatic disease. We will enroll children who exhibit any symptoms of malaria that have prompted seeking medical attention as this circumstance is the most representative of real life conditions for malaria therapy.

*Weight≥5kg.* AP is approved for children weighing greater than or equal to 5 kg.

*Positive malaria smear for P. falciparum mono-infection* with parasite density 2,000-200,000/mm3. Non-falciparum plasmodium species are generally susceptible to chloroquine and are not the focus of this study. Very low level parasitemia is more likely to be an asymptomatic infection with a different etiology of the presenting symptoms. It may be misleading to assess efficacy when the parasites are unlikely to be causing the illness. More than 200,000 parasites/mm3 may meet the criteria for severe disease and the participant should be reviewed and treated emergently and potentially referred to the hospital, rather than going through the enrollment procedures.

*Planning to remain in the study area for 1 year and willingness to return for four-weekly routine visits, as well as unscheduled sick visits.* This study requires frequent follow-up and easy access to the clinic for evaluations of every illness. Parents/guardians and children who choose to participate in the study must understand and commit to these requirements.

## Subject Exclusion Criteria

Potential participants who meet any of the following exclusion criteria at the time of evaluation for enrollment will not be eligible for enrollment in this study.

- Signs of severe malaria: One or more of the following:
  - hemoglobin ≤5 g/dL
  - prostration
  - respiratory distress
  - bleeding
  - recent seizures, coma or obtundation (Blantyre coma score < 5)
  - inability to drink
  - persistent vomiting
- Known allergy or history of adverse reaction to CQ, artesunate, azithromycin, erythromycin or AP
- Chronic medication with any antibiotic or anti malarial medication
- Previous enrollment in this study
- Alanine aminotransferase (ALT) more than 5x the upper limit of normal or creatinine greater than 3x the upper limit of normal
- Evidence of chronic disease or physical stigmata of severe malnutrition (i.e., loss of muscle mass or subcutaneous tissue, edema, or skin or hair findings consistent with severe malnutrition)

### Rationale for Exclusion Criteria

*Signs of severe malaria.* Children who are too ill to be managed at the outpatient research clinic will be referred to the hospital for management of their severe disease. Once enrolled in the study, children who develop severe malaria will be managed at the pediatric research ward at the referral hospital, but will remain in the study.

*Chronic medication with any antibiotic or antimalarial medication.* Participants who are chronically medicated with a drug that has antimalarial activity (defined as administration of a drug for more than 14 days) will have a decreased risk of acquiring malaria. This medication will interfere with our primary measure of annual incidence of malaria.

*Previous enrollment in this study.* Children who have been enrolled in the study may be infected with parasites that do not reflect the general circulating parasite genetics. Children who have completed the study or have been terminated from the study are not eligible to enroll again.

*Laboratory values more than 3-5x the upper limit of normal.* Abnormal liver and kidney function will interfere with our ability to assess the safety of the study drugs. Because the children will be acutely ill upon recruitment, moderate laboratory abnormalities may be due to acute illness, especially mildly elevated liver enzymes. Overt signs of hepatic or renal failure will be exclusion criteria (described below). Normal values for children based on studies in southern Mozambique will be used (Quinto, et al. Tropical Medicine and International Health submitted, 2006). The exact values to be used are listed in Appendix III.

*Evidence of chronic disease or severe malnutrition.* Children who have underlying illnesses may be difficult to assess for clinical cure from malaria. In addition, children with a chronic progressive disease may be mistakenly determined to have adverse effects of the drugs.

## Recruitment

Children who are brought to the Ndirande Health Centre with symptoms suggestive of malaria will be invited for evaluation at the BMP Research Clinic at the Ndirande Health Centre. There, a blood smear will be obtained and a hemoglobin level will be checked, according to standard management in Malawi. Children with uncomplicated malaria with a parasite density that may fall within the inclusion criteria and meet other eligibility criteria will be offered to participate in screening and potentially enroll in the study. Once the informed consent process has been completed and the subject’s parent/guardian has given consent, further screening and evaluation will take place, as described in the study procedures above.

## Treatment Assignment Procedures

### Randomization Procedures

The randomization scheme will be generated by the EMMES Corporation. The study statistician has no contact with participants or the study staff that cares for the participants. Treatment assignments will be generated in randomized blocks. The randomization assignment will contain a schedule for one time point to obtain chloroquine levels from day 0 through day 28. The schedule will be the same for each treatment episode. PIDs will be retired as they are assigned to subjects and not re-assigned if a participant becomes ineligible or drops out between the time of enrollment and first drug administration.

The randomization code will be kept in a secure area by the data manager in Blantyre, as well as the EMMES Corporation.

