- The prevalence of parasites with the mutation *pfcrt* 76T in cases of recurrent parasitemia after therapy

Because the genetic marker for CQ resistance is well-defined, we have the unique opportunity to assess not just resistance that is manifest on the clinical level, which may be confounded by acquired immunity, but also on the molecular level.

1. To assess the effect of each treatment arm on anemia at the end of study participation.

- Hemoglobin level without parasitemia at the close of the study

Childhood anemia is multifactorial in impoverished regions in sub-Saharan Africa and leads directly and indirectly to increased morbidity and mortality. Malaria is an important contributor to this pervasive problem (54). In our effort to simulate the public health implications of various antimalarial drug policies, we will attempt to assess the effect of each treatment arm on the general well-being of the children by measuring rates of anemia at the close of the study. We will not use the hemoglobin level at the start of the study as a point of comparison because all children will be enrolled with an episode of malaria, which will often be an acute cause of anemia. We will compare the prevalence of anemia, defined as hemoglobin <8 g/dL, at the end of one year of follow-up among all four arms.

1. To assess the safety of repeated use of the drugs in each of the study arms.

- Renal and hepatic function
- Neurological examination

Some of these medications have been associated with mild, transient abnormalities in hepatic and renal laboratory tests. We will assess these side effects in the context of repeated dosing over the course of the year. In addition, we will monitor the neurologic function of the participants due to the unique concerns associated with artemisinin derivatives.

1. To determine the chloroquine blood levels at which chloroquine sensitive and resistant parasites are able to cause infection.

- Chloroquine pharmacokinetic curve for the population
- Drug concentration at the time of parasitemia

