## Follow-up

Follow-up visits may be one of four types: day of new malaria episode diagnosis, drug efficacy follow-up, routine visit, unscheduled visit.

On the initial day of a new diagnosis, a venipuncture will be performed to obtain the following studies: filter paper sample for molecular analysis, CBC, ALT, creatinine, chloroquine level and specimen for cryopreservation of parasites. The total volume will be approximately 3.5-5 mL.

Drug efficacy follow-up occurs after the initial and all subsequent administrations of the study drug to treat symptomatic malaria. Visits will occur on days 1, 2, 3, 7, 14, 21, 28. Hemoglobin, malaria smears and filter papers will be obtained on each of those days and a physical examination will be completed. Specimens from a finger prick will be obtained on two occasions after day 0: on day 14 and an additional day assigned randomly at enrollment. Chloroquine level, CBC, ALT and creatinine will be measured routinely on day 14, after acute changes associated with malaria should have resolved If the participant misses the visit corresponding to the day a chloroquine level and/or CBC, ALT and creatinine arescheduled to be collected, the study team will endeavor to collect this specimen as the next visit. Drug administration will occur on days 1 (2nd dose) and 2 (3rd dose).If treatment failure occurs after day 3 and the parasite density is >10,000/mm3, blood will be collected to measure the chloroquine level and for cryopreservation of malaria parasites for further in vitro susceptibility testing. A neurologic exam will occur on day 28.

Routine visits occur every four weeks. Malaria smear and filter paper will be obtained. The malaria smear will be read at that time only if there are complaints of an illness or the clinician suspects malaria. The encounter will include an interval history, questions about off-study drug use, recent travel, bed net use and a physical examination. At routine visits 4, 8 and 13, CBC, ALT and creatinine will be obtained for safety monitoring surveillance. All blood specimens will be collected from a finger prick except for the specimens for cryopreservation which require 3-5 ml. On all other days, the amount of blood drawn from the finger prick will range from 0.05 ml (malaria smear, hemoglobin, filter paper) to approximately 0.5 ml (malaria smear, hemoglobin, filter paper, CBC, ALT, creatinine and chloroquine level).

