## Sample Size Considerations

In a previous longitudinal study of malaria in this population, we found that the mean annual incidence of malaria was approximately 2.5 episodes per year (59) with a standard deviation of approximately 2. Chloroquine is presently highly effective in treating malaria and has a prolonged prophylactic effect, so we have estimated a mean rate of 1.5 malaria episodes per year with chloroquine alone. We derived the sample size required to detect a decrease in the mean to 1.0 episodes per year assuming a Poisson distribution and using a 2 sided test with alpha= .05/3=.0166. The test size was adjusted to accommodate the 3 treatment versus control comparisons. With the above requirements and for a 2 treatment contrast, 120 subjects with complete observation are required per treatment arm to have 90% power (PASS 2005). To account for migration and other causes of attrition, we will enroll an additional 33% (40 subjects) in each regimen. We will accrue 160 per arm for a total of 640 subjects.

Because of the currently estimated efficacy of chloroquine alone in Malawi (in excess of 95%), we are unlikely to determine differences in initial administration (day 28) efficacy between the treatment arms. Power is limited as all arms should have very few early failures. Rates of anemia (<8 mg/dl) at the end of one year should be available in ~120 subjects per arm. The 95% CI half-width for the difference in anemia rates, calculating the variance with a rate of .2, is approximately .10. Thus, the selected sample size should be informative about larger treatment arm differences in anemia rates.

To determine the population pharmacokinetic curve for chloroquine, we have designed a randomized unbalanced study. All participants will have chloroquine levels determined prior to drug administration, at day 14 and at one additional randomly assigned time point. The assignment will be weighted to increase measurement on day two. Planned Interim Analyses

The DSMB will decide when it would like to conduct the interim analysis. The data to be reviewed at this meeting will include safety and efficacy data.

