Appendix

Appendix I: Schedule of events

Schedule of events: Enrollment and each episode of malaria

S=Standard of care

R=Research activity

| Day of Study → | 0 | 1 | 2 | 3 | 7 | 14 | 21 | 28 | Unscheduled visit  (before d28) |
| --- | --- | --- | --- | --- | --- | --- | --- | --- | --- |
| Procedure ↓ |  |  |  |  |  |  |  |  |  |
| Informed consent (enrollment only) | R |  |  |  |  |  |  |  |  |
| History-comprehensive | S | Ra | Ra | Ra | Ra | Ra | Ra | Ra | S |
| History-possible adverse drug events and recent history |  | R | R | R | R | R | R | R | S |
| Questioning about antimalarial drug use | S | R | R | R | R | S | R | R | S |
| Physical examination | S | R | R | R | R | R | R | R | S |
| Neurological examination |  |  |  |  |  |  |  | R |  |
| Finger stick blood sample for malaria smear and hemoglobin. | S | Ra | R | R | R | R | R | R | S |
| Venous blood draw (parasite cryopreservation) | R |  |  |  | Rb | R b | Rb | Rb | Rb |
| CBC, ALT, creatinine | R |  |  |  |  | R |  |  |  |
| Finger stick blood sample for drug levels (r= at one of these time points only, research activity) | rc |  | rc | r | r | r | r | r | Rb |
| Assignment of study treatment group | R |  |  |  |  |  |  |  |  |
| Administration of drug | S | R | R |  |  |  |  |  |  |
| GPS mapping of house and household survey (enrollment only or if participant moves) | R |  |  |  |  |  |  |  |  |

a As clinically indicated. Visits are part of research protocol but investigations of complaints are standard clinical care.

b In cases of parasite density>10,000/mm3

rParticipants randomly assigned to have blood drawn on two of these days

cParticipants asked to return three hours after dose

Schedule of events: Routine visits and unscheduled visits (if malaria is diagnosed at any visit, follow schedule listed above)

|  | Routine visit 0-13b | Unscheduled visitc |
| --- | --- | --- |
| History-comprehensive | R | S |
| Questioning about medication use | R | S |
| Questioning about recent travel and bednet use | R |  |
| Physical examination | R | S |
| Malaria smear | R | S a |
| CBC, ALT, Creatinine, Neurological examination | Visits number 4, 8 and 13 |  |
| Additional evaluations | S a | S a |
| Counseling about next visit | R | R/S |

a As clinically indicated

bSame procedure as premature termination visit

cIf malaria is diagnosed, see schedule for malaria episode

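### Appendix I contradicts itself and Sections 7.3 and 11.2 on which chloroquine levels every child has drawn

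*Protocol*

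**What the plan says.** The statistical section (11.2) states the design most fully: "All participants will have chloroquine levels determined prior to drug administration, at day 14 and at one additional randomly assigned time point". It continues: "The assignment will be weighted to increase measurement on day two".

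Section 7.3 agrees. On the day of each new diagnosis the venipuncture covers "CBC, ALT, creatinine, chloroquine level and specimen for cryopreservation of parasites". After day 0, finger-prick specimens follow "on day 14 and an additional day assigned randomly at enrollment", and the same paragraph lists the chloroquine level among the routine day-14 tests. Section 7.2 takes a chloroquine level at enrollment, before any drug is given.

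Section 5.4.1 covers the random part: "The randomization assignment will contain a schedule for one time point to obtain chloroquine levels from day 0 through day 28". It then fixes that part across episodes: "The schedule will be the same for each treatment episode".

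Appendix I has one row for drug levels, collected by finger stick. Its label reads "r= at one of these time points only, research activity". The lower-case r stands under days 0, 2, 3, 7, 14, 21 and 28. The footnote to that symbol says that children are randomly assigned to two of the days. A further footnote, on days 0 and 2, asks families to come back three hours after the dose. No row shows a drug level before dosing for all children: the venous row is labelled for parasite cryopreservation only.

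The outcome measure that these samples serve, under secondary objective 6, is "Chloroquine pharmacokinetic curve for the population".

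**The concern.** Sections 7 and 8 both name Appendix I as the schedule, so it is what clinic staff are likely to work from. On three counts it does not match the text: the number of random days (and here it also contradicts itself), whether day 14 is fixed or random, and whether every child has a level before dosing.

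The pre-dose and day-14 levels are the two points that Section 11.2 plans to have in every child. Section 3.2.2 uses the population curve to predict, after the event, the level at which parasites were able to grow. A level that is not drawn cannot be recovered. The make-up rule in Section 7.3 covers a missed visit for which a sample was scheduled. It does not help a child who attends on day 14 but is not listed for a drug level.

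**Working it through.** The Protocol gives no sample size, power or precision for the chloroquine curve, so there is no figure to reproduce. The check sets the places side by side and counts what each would collect per episode, leaving aside the extra level at treatment failure.

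| Place in the Protocol | Day-0 level in all | Day 14 | Random days | Levels per episode |
| --- | --- | --- | --- | --- |
| 5.4.1 | not addressed | not addressed | 1 | 1 random |
| 7.3 | yes, day of diagnosis | all children | 1 | 3 |
| 11.2 | yes, before dosing | all children | 1, weighted to day 2 | 3 |
| Appendix I, row label | none shown | random option | 1 | 1 |
| Appendix I, footnote r | none shown | random option | 2 | 2 |

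Share of children with a day-14 level if Appendix I is followed as written:

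- Inputs: seven days marked r (Appendix I) and 640 children (Section 11.2). Equal choice among the days is an assumption.
- One random day: 1/7 = 14.3%, or 640/7 ≈ 91 children.
- Two different random days: 2/7 = 28.6%, or 640 × 2/7 ≈ 183 children.
- Sections 7.3 and 11.2: 100%, or 640 children.

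Section 11.2 weights the draw towards day 2 but does not say by how much. Taking a threefold weight as an illustration, the weights sum to 3 + 6 = 9:

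- One day: 1/9 = 11.1%.
- Two days, drawn in turn without replacement: 1/9 + (3/9)(1/6) + (5/9)(1/8) = 0.111 + 0.056 + 0.069 = 23.6%.

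The range over these readings is therefore about 11% to 29%, against 100%. Because Section 5.4.1 keeps the same schedule at every episode, a child without a day-14 slot would have none at later episodes either.

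For the pre-dose level, the Appendix I drug-level row alone yields none: its only day-0 entry is random and follows the dose by three hours.

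**The case against.** The best defence is that the text is clear and only the table is loose. Sections 5.4.1, 7.3 and 11.2 and the Appendix I row label all give one random day. The two in the footnote matches the count in Section 7.3 of two occasions after day 0, if one of them is taken to be day 14. The pre-dose level comes by venipuncture, so it has no place in a finger-stick row. Staff who also read Section 7.3 would draw the right samples.

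Much of this stands. It shows which rule the Protocol intends and makes the fault one of transcription. It does not remove the fault: the footnote makes both days random, day 14 carries the random symbol, and no row of the table shows a chloroquine level before dosing.

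A reader might infer four stronger things that the documents do not support.

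- That Section 5.4.1 is itself in conflict. Its single time point is naturally the random one; fixed samples need no randomization.
- That pre-dose and three-hour levels exclude each other. They can be two samples, the second only for children whose random slot is day 0 or day 2.
- That some children would have a duplicate day-14 sample. Section 7.3 calls the random day additional, so under the text it is another day.
- That reusing the random day leaves each child's curve poorly estimated and so defeats objective 6. The stated measure is a population curve, and no individual curve is promised. Section 7.3 also takes a level at every new diagnosis, which is a late point on the previous course. In an illustrative log-linear model (half-life 8.5 days; between-child CV 30% for slope and 40% for level; residual 25-40%; two or three episodes), re-drawing the day and dropping day 14 from the random set gives 0.66-0.88 of the variance of a child's predicted day-35 log level when those late levels are left out. It gives 0.92-0.99 once one is added per recurrence at an assumed 35, 45 or 60 days.

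**Conclusion.** The point holds for Appendix I. It contradicts itself on the number of random days. It also contradicts Sections 7.3 and 11.2 on the day-14 level, and it omits the universal pre-dose level. Followed literally, it would give a day-14 level in about 14% or 29% of children under equal choice, or about 11% or 24% under an assumed threefold weight on day 2, where the text plans 100%. These are the shares under a literal reading of the table; staff who also follow Section 7.3 would lose less.

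The primary outcome is not touched, and the population curve remains estimable under the schedule in Section 11.2. With the random day reused and spread evenly over six days, about 107 children (640/6) fall on each day. Assuming a between-child SD of 0.3-0.7 and a residual SD of 0.2-0.4 on the log scale, and 2.5 treated episodes per child, the standard error of the mean log level per day is 0.032-0.072. Re-drawing the day would lower this to 0.022-0.049. That is an efficiency gain the sponsor may consider, not the correction of an error.

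**What to change.** Reconcile Appendix I with Sections 7.3 and 11.2:

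- Mark a chloroquine level before dosing on day 0, and one on day 14, as R for all children.
- Remove day 14 from the set of random days.
- Make the row label and footnote r both say one additional random day.
- State that the three-hour footnote applies only to that random draw when it falls on day 0 or day 2.

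In Section 5.4.1, add at most a clause saying that its one time point comes on top of the fixed samples. Re-drawing the random day at each episode is optional and would need only a longer list in the randomization file.

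The cost is a corrected table and a sentence. It needs no blood and no visits beyond Sections 7.3 and 11.2, and Appendix I already schedules CBC, ALT and creatinine on days 0 and 14. The correction has to reach the clinic before sampling, because levels not drawn cannot be replaced.
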